**Materials and Methods**

The *Improving Mood* study was a 5-year, two arm, parallel randomized controlled trial (RCT) that compared the speed of processing training program known as *Road Tour* to attention control using computerized crossword puzzles in assisted living (AL) and related senior living settings. Three specific aims evaluated the effect of *Road Tour* vs. attention control on: (1) cognitive processing speed; (2) reducing depressive symptoms and the risk of onset of suspected clinical depression; and, (3) depression-related comorbidities including anxiety, pain, and health-related quality of life among older adults living in AL.

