***Setting recruitment and engagement***

A community-based research approach was used to engage AL settings as partners in conducting the research project. The goal was to engage up to 30 AL settings that would each recruit a minimum of 10 older adult participants to achieve the target of 300 total participants. As partners in the research, each organization identified one or more staff members who completed university-sponsored, online human subjects training and acted as onsite research assistants (RAs). These onsite RAs, called Study Liaisons, were trained to recruit, consent, and train participants to use the computer games, conduct computer-based assessments, and facilitate telephone assessments conducted by university team members. Study Liaison preparation used detailed training manuals and fidelity checks performed by the Study Coordinator to assure the integrity of study procedures at partner sites.

Adaptation: Although AL programs were plentiful, the vast majority were too small to identify 10 participants who would participate, and/or didn’t have staff resources to support the participatory study approach. Moreover, senior living leaders questioned the logic of involving only AL residents, noting that many residents on the same campus were “one service away” from being classified as “assisted” based on their age, health, and function. Others indicated that they had abandoned policies that required residents to relocate when they needed services. In turn, many older adults living in housing that was defined as “independent living” (IL) on their campus were receiving personal assistance similar to those living in housing defined as AL. As a result, older adults residing in IL apartments on senior living campuses whose AL services were also involved in the study were also invited to participate.

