***Experimental Design***

[figure not shown]

Eligible older adults who completed informed consent with Study Liaisons were scheduled for baseline telephone interviews conducted by university team members. All primary outcome measures were collected via telephone interviews, except for the speed of processing measure (Useful Field of View, UFOV) which was collected onsite by Study Liaisons. Randomization occurred after baseline interviews were completed. Participants were asked to complete 10 hours of training during the first 5-6 weeks, and 4 additional hours of training at 5 and 11 months for a total targeted dose of 18 hours.

**Randomization.** Participants were randomized to training groups using block randomization within sites and types of care (AL and IL) to maintain balance across treatment conditions by senior living community and residence type (AL and IL). The study statistician determined the order of assignments using a computer-generated list of random numbers using block sizes of two and four. Participant IDs and assignments were concealed in sequentially numbered opaque envelopes stored in separate bins (one for each site) kept in a locked cabinet within the Study Coordinator’s office.

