***Analysis***

Descriptive statistics including Student’s t-tests and chi-squared analysis are used to compare the intervention and attention control groups at baseline, and to examine differences based on living setting (AL vs. IL). The original analysis plan was to evaluate the three specific aims using each person serving as his/her own control in linear panel analyses ^20^ with GEE to correct for clustering within sites, and, logistic regression GEE models for binary outcomes. Power estimates were based on the results from the earlier *IHAMS* and *ACTIVE* studies. Setting a one-tailed *α* at 0.05 and allowing for 10% attrition, we estimated > 80% power to detect the improvements in *UFOV*, 73% power to detect changes in depressive symptoms and 68% power to detect suspected onset of clinical depression.

Adaptations. Because of the inclusion of participants from IL settings, the analytic approach will be altered. We will use random effects general linear mixed models. The dependent variable will be the outcome of interest at the time point of interest. The clustering (random effects) variable will be the AL or IL from each participating senior living community. The two main factors will be intervention vs. attention control and AL vs. IL. The interaction between these two factors will be included to test for heterogeneity of treatment effects (HTEs) between AL vs. IL. Covariates will include the outcome of interest at baseline, age, and sex.

Two *ad hoc* analyses for the first specific aim will also be conducted. The first will involve expanding the intervention vs. attention control from a binary indicator to a trichotomous indicator of *Road Tour* vs. *Double Decision* vs. attention control to test for potential HTEs between the two speed of processing platforms. The second will involve opportunistic dosing testing based on whether the intervention participants completed eight or more hours of intervention training vs. less than eight hours.

References

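### The sole efficacy model carries the arm-by-setting interaction and names no overall-effect test, so its intervention term need not be the effect over all randomised participants

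*Protocol*

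**What the plan says.** Under Materials and Methods, the Protocol frames its three aims as comparisons of the speed-of-processing programme with the crossword control. The end of that sentence places the population in assisted living: "health-related quality of life among older adults living in AL". Under Setting recruitment and engagement, an adaptation later admits independent-living residents of the same campuses.

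Under Analysis, the Adaptations paragraph replaces the original linear panel/GEE approach with a random-effects mixed model, because IL residents were included. Its fixed part is described so: "The two main factors will be intervention vs. attention control and AL vs. IL". It continues: "The interaction between these two factors will be included to test for heterogeneity of treatment effects (HTEs) between AL vs. IL". The remaining terms are the baseline value of the outcome, age, sex, and a random effect for each community's AL or IL unit.

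The section gives no second model without the interaction, no averaged contrast, no factor coding and no rule for dropping the interaction. The only other efficacy analyses are two ad hoc ones for Aim 1 (software platform, and hours of training completed). The power figures stand with the original GEE plan and are not restated for the altered model.

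**The concern.** The interaction has one declared purpose, the heterogeneity test, but it sits in the only model from which a treatment effect can be read. Once it is there, the term labelled intervention changes meaning with the coding of the setting factor. One fitted model can then yield an AL effect, an IL effect, an equally weighted average or an effect weighted by enrolment, each with its own p-value and confidence interval. The Protocol does not say which answers the aims.

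Two things are at stake. The headline result could describe one setting, or a mix that was not enrolled, while being reported as the trial's effect. It could also be less precise than the randomised comparison over all participants, in a trial where two of the three stated powers are already below 80%.

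**Working it through.** **Inputs from the Protocol**

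- Test level and attrition (Analysis): "Setting a one-tailed *α* at 0.05 and allowing for 10% attrition".
- Stated power (Analysis): above 80% for UFOV, then "73% power to detect changes in depressive symptoms and 68% power to detect suspected onset of clinical depression".
- Sample size (Setting recruitment and engagement): "to achieve the target of 300 total participants". After attrition, 300 × 0.90 = 270, or 135 per arm.
- Allocation (Experimental Design, Randomization): within site and type of care, "using block sizes of two and four". The ratio is not stated. I assume 1:1, roughly balanced within each setting.
- AL:IL split: not given. I assume a reference-setting share *p* between 0.2 and 0.8.

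**The plan's own figure.** The stated powers cannot be reproduced, because no effect size, SD, event rate or intraclass correlation is given. They can only be inverted. With noncentrality δ = z(0.95) + z(power), and more than 80% taken as 80%:

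- 80%: 1.645 + 0.842 ≈ 2.486
- 73%: 1.645 + 0.613 = 2.258
- 68%: 1.645 + 0.468 = 2.113

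Under a two-means approximation, d = δ√(2/135), so these correspond to standardised differences of 0.303, 0.275 and 0.257. This is a back-solution and does not confirm the plan's figures.

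**Variance of each candidate effect.** Take *N* analysed participants, arms balanced within setting, and residual variance σ².

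- Overall effect, no interaction: 4σ²/N.
- Arm term, 0/1 coding (reference setting only): 4σ²/(Np). Relative information is *p*.
- Arm term, sum-to-zero coding (equal-weight average): ¼[4σ²/(Np) + 4σ²/(N(1−p))] = σ²/(Np(1−p)). Relative information is 4p(1−p).
- Contrast weighted by enrolled shares, from the interaction model: p²·4σ²/(Np) + (1−p)²·4σ²/(N(1−p)) = 4σ²/N. Relative information is 1.

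The first two ratios were checked against least-squares design matrices at p = 0.2, 0.5 and 0.8 and agreed (0.20, 0.50, 0.80 and 0.64, 1.00, 0.64). The unit-level random effect and the covariates are left out. Because randomisation is within site and type of care, they act about equally on both models and change the ratios little.

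**Information loss relative to the overall effect**

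| Reference share p | 0/1 coding, 1 − p | Sum-to-zero coding, 1 − 4p(1−p) |
|---|---|---|
| 0.2 | 80% | 36% |
| 0.3 | 70% | 16% |
| 0.5 | 50% | 0% |
| 0.7 | 30% | 16% |
| 0.8 | 20% | 36% |

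Under sum-to-zero coding the loss reaches one half only when one setting holds about 15% or less (p = 0.5 − 0.5√0.5 = 0.146).

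**Illustration in power.** With equal effects in AL and IL, power = Φ(δ√(relative information) − 1.645). For 80% under 0/1 coding at p = 0.5: 2.486 × 0.707 = 1.758, and Φ(1.758 − 1.645) = 0.545.

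| Case | UFOV | Depressive symptoms | Onset of suspected depression |
|---|---|---|---|
| No interaction, or share-weighted contrast | 80% | 73% | 68% |
| 0/1, p = 0.5 | 54.5% | 48.1% | 44.0% |
| 0/1, p = 0.2 | 29.7% | 26.3% | 24.2% |
| 0/1, p = 0.8 | 71.9% | 64.6% | 59.7% |
| Sum-to-zero, p = 0.5 | 80% | 73% | 68% |
| Sum-to-zero, p = 0.2 or 0.8 | 63.5% | 56.4% | 51.8% |

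**The case against.** The strongest reply is that the Protocol nowhere says a reference-coded coefficient will be the main result. It calls arm and setting the main factors and gives the interaction a limited job, which fits an ordinary factorial reading: marginal main effects plus an interaction test. Coding and contrasts are commonly left to a statistical analysis plan, which is not at hand. This stands in part. The missing coding is not in itself a fault. What the Protocol does fix is a single efficacy model with the heterogeneity term inside it, and that choice can be improved whatever a later document adds.

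A reader might infer that the interaction itself costs information, or that the loss is capped at about half. The documents support neither. The share-weighted contrast from the same model loses nothing, so the loss comes from how the arm term is read. Half is the value for 0/1 coding at an even split and is not a bound.

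A reader might also infer that the trial's real power is about 55/48/44%. That does not follow. The stated powers belong to the GEE plan, UFOV is given only as above 80%, and neither the coding nor the split is known.

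Finally, the pooled effect is not self-evidently the target. The aims sentence names AL residents, so with AL as the reference the 0/1 arm term arguably fits that wording, although the same section also mentions related senior living settings. This objection stands: the target population is unsettled and has to be stated.

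**Conclusion.** The point holds in a limited form. The Protocol places a term meant only for a heterogeneity test in its sole efficacy model for all aims and names no overall-effect test. The intervention term then need not be the effect over all randomised participants.

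The size depends on two facts that the Protocol does not give, the AL:IL split and the coding. The ranges above rest on the assumed 20% to 80% reference share and on arms balanced within setting. The power figures also need equal effects in both settings and are illustrative only. The change is worth making because it is cheap and removes a post hoc choice between contrasts. It is not a must-fix error, and the text does not show that a wrong effect would be reported.

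**What to change.** 1. Take the treatment effect for each aim from the mixed model with arm, AL/IL, baseline outcome, age, sex and the random intercept for the site-by-setting unit, without the interaction. A pre-stated contrast weighted by the enrolled AL and IL shares, taken from the interaction model, is an equally valid alternative.
2. Test arm by AL/IL in a separate model used only for heterogeneity. Report the AL-specific and IL-specific effects from it with confidence intervals, labelled exploratory.
3. State that the target population is all randomised AL and IL participants, and bring the aims wording under Materials and Methods into line.

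The cost is a few sentences of text and one extra model fit per outcome. No further data are needed.

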Adaptation. Posit Science Corporation’s CD-ROM based *Road Tour* training program was used until support was unexpectedly discontinued in August 2014, roughly 17 months after starting enrollment. The web-based replacement, *Double Decision*, (<https://www.brainhq.com/why-brainhq/about-the-brainhq-exercises/attention/double-decison>) was used from 2014 through the end of enrollment in 2015. The training features of *Double Decision* are the same as *Road Tour* (as described above). The transition to *Double Decision* presented short-term delays as we developed new recruitment and training materials for *Double Decision* and negotiated support for participants already using *Road Tour* to assure use of one format or the other, but not both by a single participant.

**Attention Control.** *Boatload of Crosswords* (<http://www./boatloadpuzzles.com>) served as the attention control condition. *Boatload of Crosswords* is one of the oldest and most popular crossword puzzle games commercially available. The software offers the user a choice between three puzzle sizes, three levels of complexity, and varying font sizes. *Boatload of Crosswords* also provides optional help features, like filling in letters and words, showing incorrect letters or words in red, and solving the puzzle, that minimize frustration levels often associated with puzzle completion. *Boatload of Crosswords* was chosen for this study because, like *Road Tour*, it is computerized, very popular and easy to use; many older adults enjoy doing crossword puzzles; and it was successfully used as the attention control condition in *IHAMS*.^6^

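### The ad hoc Road Tour vs Double Decision test pools controls over calendar time, so unexplained drift in follow-up UFOV would read as a platform effect

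*Protocol*

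**What the plan says.** **Platform and calendar time.** Under Intervention and Attention Control Training Programs (Adaptation), the Protocol says that Road Tour "was used until support was unexpectedly discontinued in August 2014, roughly 17 months after starting enrollment". Its web-based replacement, Double Decision, "was used from 2014 through the end of enrollment in 2015". The transition was managed "to assure use of one format or the other, but not both by a single participant".

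**Randomisation.** Under Experimental Design, participants are allocated only to intervention or attention control, blocked within site and type of care, "using block sizes of two and four". Platform is not a randomised factor.

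**Platform analysis.** Under Analysis, the first of two ad hoc analyses for Aim 1 consists of "expanding the intervention vs. attention control from a binary indicator to a trichotomous indicator". Its levels and purpose are given as a "trichotomous indicator of *Road Tour* vs. *Double Decision* vs. attention control to test for potential HTEs between the two speed of processing platforms".

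**Model.** The same section specifies a mixed model with arm, AL vs IL and their interaction. It adds the baseline outcome, age and sex as covariates, and a random effect for each community's AL or IL unit. It names no enrolment date, period term or restriction to concurrent controls.

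**The concern.** Heterogeneity of treatment effect between platforms is the difference between two treatment-versus-control effects. Here each platform belongs to its own stretch of enrolment, but both are referred to one control group spanning the whole of it. That control group drops out of the platform contrast. What remains is a before/after comparison of intervention participants, which randomisation does not protect.

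UFOV is the outcome concerned. It is collected on site by Study Liaisons and not by the central telephone interviewers, so changes over time in sites or liaisons could reach it. The Protocol also says that recruitment and training materials were redeveloped at the switch.

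The analysis is the only empirical check in the Protocol on treating the two platforms as one intervention. A spurious difference would wrongly undermine that pooling, and a masked difference would wrongly support it.

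**Working it through.** The Protocol gives no power or precision figure for this contrast, so there is none to reproduce. Its power statement covers UFOV, depressive symptoms and onset of suspected depression in the two-arm comparison.

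**Inputs from the Protocol**
- Target 300 participants (Setting recruitment and engagement) and 10% attrition (Analysis): 300 x 0.9 = 270 completers.
- 1:1 allocation, inferred from the block sizes because no ratio is stated: 135 intervention completers.
- UFOV SD 247.5 ms from the cited norms (Instruments and Measures).

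**Assumptions not in the Protocol**
- A drift D in follow-up UFOV, the same in both arms and not explained by the model.
- A share w of participants in the Road Tour period.
- A proportion R2 of variance explained by the covariates.
- A two-sided 5% test and no true platform difference.

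**Step 1: bias.** Set the earlier period to 0 and the later one to D. The pooled control mean is then (1-w)D.
- Road Tour minus control: 0 - (1-w)D = -(1-w)D
- Double Decision minus control: D - (1-w)D = wD
- Double Decision minus Road Tour: D

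With w = 0.6 and D = 50 ms, the biases are -20, +30 and 50 ms. Against concurrent controls, the common drift cancels: (D - D) - (0 - 0) = 0.

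**Step 2: false-positive rate.** Split the 135 as 67 and 68. In SD units, SE = sqrt((1-R2)(1/67 + 1/68)), which is 0.172 at R2 = 0 and 0.138 at R2 = 0.36. The rejection probability is Phi(D/SE - 1.96) + Phi(-D/SE - 1.96).

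| Drift | R2 = 0 | R2 = 0.36 |
|---|---|---|
| 0.1 SD (24.75 ms) | about 9% | about 11% |
| 0.2 SD (49.5 ms) | about 21% | about 31% |

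The R2 = 0.36 column holds D fixed while the SE shrinks. It therefore applies only if the drift arises after baseline and is unrelated to it.

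**Step 3: does the random effect rescue the contrast?** A random-intercept REML model was simulated with 2,000 runs per scenario, residual SD 0.8 x 247.5 = 198 ms and w = 0.6. ICC was 0.03 unless stated. Baseline, age and sex entered only through the reduced residual SD.

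| Scenario | Spurious difference | False positives |
|---|---|---|
| No drift | about 0-1 ms | 5.6% |
| D = 50 ms, sites enrol in both periods | 50 ms | 30% |
| D = 50 ms, each site in one period | 48 ms | 27% |
| D = 50 ms, each site in one period, ICC 0.10 | 38 ms | 18% |

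The random effect removes only part of the bias. With period added alongside the platform terms, the mean spurious difference stayed within about 3 ms of zero, and false positives were 4.4% to 6.4% in every scenario.

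**Step 4: cost in precision.** The arm x period contrast uses four cells of about 67.5: SE = sqrt(4/67.5) = 0.243 SD at R2 = 0. The ratio is 0.243/0.172 = 1.41.

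**The case against.** The strongest reply is that the model already adjusts for much of what might drift. AL/IL is a factor, age, sex and baseline UFOV are covariates, and the unit random effect absorbs part of any site difference. UFOV is also computer administered and automatically scored, so a stable shift from hardware or liaisons would appear at baseline too. This stands, and it limits the point to drift that these terms leave unexplained.

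A reader might infer that the admission of IL residents and the lower age limit show up as platform effects. The documents do not support that: neither change is dated, and AL/IL and age are both in the model. Nor does the Protocol say which sites recruited in which period.

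A reader might also infer that the main results are biased. They are not affected in this way, because blocked randomisation within site and care type tends to balance the arms over time.

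Two further replies are that the analysis is labelled ad hoc and that detail may sit in an SAP. The first limits how much the point matters. The second does not remove it, because the Protocol itself specifies the three-level indicator with a single control level, and the problem lies in that coding.

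**Conclusion.** The point holds for the ad hoc Aim 1 platform analysis. As specified, it tests Road Tour against Double Decision across periods, and each platform-versus-control contrast uses partly non-concurrent controls. This follows from the design and does not depend on any assumed number.

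The size of the problem is unknown, because no drift is reported. The 9-31% range is conditional on an unexplained drift of 0.1 to 0.2 SD, an even split and R2 of 0 to 0.36. It is not an estimate of the error rate in this trial. With each site confined to one period and ICC 0.10, the simulated rate at 50 ms was 18%.

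It would also be too strong to say that concurrent controls remove all bias. They remove drift common to both arms. If the treatment effect itself changed over time, for instance through adherence or liaison skill, that change remains inseparable from platform.

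**What to change.** Replace the three-level indicator:
- Classify every participant, controls included, by the platform period in force at randomisation.
- Fit arm + period + arm x period with the planned AL/IL factor, covariates and random effect.
- Use arm x period as the test of platform heterogeneity.
- Report Road Tour and Double Decision each against its concurrent controls, with intervals.
- Label the result exploratory and non-randomised for platform, and state that a treatment effect varying over time stays confounded with platform.

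This needs revised analysis wording and the randomisation dates. Concurrent controls should exist in both periods, because allocation was in small blocks within site and care type. The cost is the wider interval shown in Step 4, equivalent to halving the sample for this contrast. A null result would therefore say little about whether the platforms are equivalent.
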